# Lung UltrasouNd Guided surfactant therapy in preterm infants: an international multicenter randomized control trial (LUNG study)

**DOI:** 10.1186/s13063-023-07745-8

**Published:** 2023-11-04

**Keywords:** Preterm infants, Lung ultrasound, Respiratory distress syndrome, Surfactant therapy

## Abstract

**Background:**

The management of respiratory distress syndrome (RDS) in premature newborns is based on different types of non-invasive respiratory support and on surfactant replacement therapy (SRT) to avoid mechanical ventilation as it may eventually result in lung damage. European guidelines currently recommend SRT only when the fraction of inspired oxygen (FiO_2_) exceeds 0.30. The literature describes that early SRT decreases the risk of bronchopulmonary dysplasia (BPD) and mortality. Lung ultrasound score (LUS) in preterm infants affected by RDS has proven to be able to predict the need for SRT and different single-center studies have shown that LUS may increase the proportion of infants that received early SRT.

Therefore, the aim of this study is to determine if the use of LUS as a decision tool for SRT in preterm infants affected by RDS allows for the reduction of the incidence of BPD or death in the study group.

**Methods/design:**

In this study, 668 spontaneously-breathing preterm infants, born at 25^+0^ to 29^+6^ weeks’ gestation, in nasal continuous positive airway pressure (nCPAP) will be randomized to receive SRT only when the FiO2 cut-off exceeds 0.3 (control group) or if the LUS score is higher than 8 or the FiO2 requirements exceed 0.3 (study group) (334 infants per arm). The primary outcome will be the difference in proportion of infants with BPD or death in the study group managed compared to the control group.

**Discussion:**

Based on previous published studies, it seems that LUS may decrease the time to administer surfactant therapy. It is known that early surfactant administration decreases BPD and mortality. Therefore, there is rationale for hypothesizing a reduction in BPD or death in the group of patients in which the decision to administer exogenous surfactant is based on lung ultrasound scores.

**Trial registration:**

ClinicalTrials.gov identifier NCT05198375. Registered on 20 January 2022.

## Background

The management goal of neonatal respiratory distress syndrome (RDS) is to improve survival of affected neonates using non-invasive respiratory support, surfactant therapy, mechanical ventilation, and overall care of the premature neonate [1].

Currently, the European consensus guidelines on RDS recommend administering surfactant in non-invasively ventilated neonates when the fraction of inspired oxygen (FiO_2_) is higher than 0.30 during nasal continuous positive airway pressure (nCPAP) of at least 6 cmH_2_O [1]. Since oxygenation depends on both FiO_2_ and mean airway pressure, the accuracy of this criterion might be suboptimal because the setting of respiratory support is not clearly standardized. Moreover, there is a large body of evidence that early exogenous surfactant administration plays a pivotal role in the treatment of RDS. In fact, in the short term, it reduces the incidence of pneumothorax. In the long term, it improves survival and, since it may allow the avoidance of invasive mechanical ventilation, minimizes the development of bronchopulmonary dysplasia (BPD) and death [2].

On the contrary, waiting to fulfill FiO_2_ criteria for surfactant replacement therapy (SRT) can lead to delayed administration and reduce the potential beneficial effects of surfactant [3, 4]. At present, there is no universal consensus on the criterion and cut-off to adopt for surfactant treatment [1, 5, 6].

The role of lung ultrasound (LU) as a semi-quantitative method to decide whether to administer exogenous surfactant has been extensively studied in recent years. The first study by Brat et al. [7] demonstrated that a LU score (LUS) quantifies RDS severity and can predict the need for SRT. This was subsequently confirmed by De Martino et al. [8]. Following these preliminary results, Raschetti et al. [3] demonstrated in a single-center quality-improvement study that the use of a LUS cut-off to guide SRT led to a significant increase of the proportion of neonates who received surfactant treatment in the optimal therapeutic window (defined as therapy carried out within the first 180 min of life), without increasing the number of treated infants. This finding has been confirmed by a recent single-center randomized controlled trial by Rodriguez-Fanjul et al. [4]. Although the adoption of LUS can enhance the quantitative diagnostic evaluation of severity of RDS and allows early identification of neonates who will later require SRT, there is not enough evidence that this significantly leads to a clinical benefit; the universal use of LUS to guide surfactant treatment outside a research setting still cannot be supported. To the best of our knowledge, there are no multicenter randomized controlled trials which evaluate short- and long-term clinical outcomes in preterm infants who receive echo-guided surfactant treatment in comparison with current treatment based on the FiO_2_ criterion.

### Trial hypothesis

We hypothesized that the use of a LUS to quantify RDS severity and guide surfactant treatment (study group) may increase the proportion of preterm infants receiving timely SRT and eventually improve their short- and long-term outcomes in comparison with a control group treated according to the FiO_2_ criterion alone.

Therefore, our hypothesis is that the study group will show a decrease in the proportion of infants affected by BPD or death.

To confirm this hypothesis, we planned an international multi-center randomized controlled study in which preterm infants are randomized into two groups: one will receive SRT based on the FiO_2_ criterion and the other will receive SRT on the basis of LUS and/or FiO_2_ cut-off.

The study flow chart is detailed in Fig. 1.

**Fig. 1 Fig1:**
[figure not shown]
Study flow chart

### Roles and responsibilities for committees

LUNG study is led by a Steering Committee comprising the senior investigator (CD), the national coordinators (IC for Italy and JRF for Spain), and two national experts (FR for Italy and MSL for Spain) who will oversee the progress and adherence of the centers to the study protocol. There will be one principal investigator in each center who will be responsible for obtaining ethical approval, organizing local Good Clinical Practice monitoring and data entry into the patient report forms.

## Methods/design

### Study design

This will be an unblinded multi-center randomized open control trial with two parallel groups of surfactant treatment based on FiO_2_ cut-off versus LUS and/or FiO_2_ cut-off in spontaneously breathing infants in nCPAP for RDS born at 25^+0^ to 29^+6^ weeks of gestational age (GA).

The financial outcome of the study is no profit. The design of the study is of superiority.

### Participating centers

The following centers are actively recruiting for the trial:

Careggi University Hospital of Florence, Florence, Italy; Germans Trias i Pujol, Badalona, Spain; Federico II University of Naples, Naples, Italy; Udine Hospital, Italy; Fondazione IRCCS Ca' Granda, Milano, Italy; Brescia Hospital, Italy; Pisa University, Italy; IRCCS AUOBO University of Bologna, Bologna, Italy; Policlínico Gemelli, Rome, Italy; Gregorio Marañon, Madrid, Spain; Basurto, Bilbao, Spain; Puerta del Mar, Cadiz, Spain; Alvaro Cunqueiro, Vigo, Spain; Clinic, Barcelona, Spain; Complexo Hospitalario Universitario de A Coruña (CHUAC), Spain; Ospedale Infermi di Rimini, Rimini, Italy; Policlinico Universitario di Modena; Bolzano Hospital, Ospedale dei Bambini “V. Buzzi” Milan, Italy.

We estimate that the participating centers will have a minimum of 10 and a maximum of 70 eligible patients during the study period in order to have a final sample size 668 children (334 per arm). Sample size calculation and trial simulation have been performed with R (see below).

The study will be carried out in third or fourth level NICUs in which medical staff is adequately trained to use LU and quantify RDS severity with LUS.

### Inclusion criteria

Infants fulfilling the following inclusion criteria will be eligible to participate:In-born at 25 + 0 to 29 + 6 weeks of gestational age.Spontaneously breathing at birth but requiring non-invasive respiratory support with nCPAP at a positive pressure of 6–8 cm H_2_O to maintain a peripheral oxygen saturation (SpO_2_) between 90 and 95%.Respiratory distress syndrome (defined as respiratory distress appearing within the first 24 h of life requiring nCPAP to keep peripheral oxygen saturation above 90%, with clinical signs of respiratory difficulty such as polypnea, chest retractions, nasal flutter in the absence of other respiratory diseases non-mandatory criterion was lung images that support the diagnosis [4]).Parental written signed consent has been obtained.

### Exclusion criteria

Endotracheal intubation in the delivery room for resuscitation or insufficient respiratory drive according to the European guidelines [1].Prolonged premature rupture of membranes (pPROM) for more than 3 days.Presence of major congenital malformations or chromosomal anomalies.Hydrops fetalis.Inherited disorders of metabolism.Administration of surfactant before performing LU.Air leak syndrome (pneumothorax, pneumomediastinum), congenital diaphragmatic hernia, congenital pneumonia, meconium aspiration syndrome.

### Sample size

The percentage from international databases of infants with GA between 25^+0^ and 29^+6^ weeks expected to die or to develop BPD derived is approximately 40% using the Jobe and Bancalari (2001) definition [9, 10].

In a retrospective analysis of our data, the percentage of composite outcome of BPD and death at participating centers was 35%.

Assuming the percentage of newborns with death or BPD is 35% (the most conservative condition) in the control group and a decrease to 25% in the experimental group, a sample size of 668 children (334 per arm) is required to obtain a statistical power of 80% with alpha 0.05.

An interim analysis will be planned after 167 infants per arm are enrolled (334 total infants enrolled). Based on the results of the interim analysis, the study will continue to be carried out as follows:1: If the statistical *Z* test gives a value equal to or less than 0.01, the study will be terminated for futility;2: If the statistical *Z* test gives a value equal to or greater than 2.75, the study will be terminated for efficacy;3: If the statistical *Z* test gives a value less than 0.41 or higher than 0.8, the study will be continued until the previously calculated sample size is equal to 668.4: If the statistical *Z* test gives a value equal to or higher than 0.41 and equal to or less than 0.8, the final sample size will be modified, but without exceeding the maximum threshold of 1.5 times the expected initial size (sample size max: 1002).

Sample size calculations and trial simulations have been performed with R.

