### Statistical analysis

Clinical characteristics of infants in the CG and LUSG will be described using mean values and standard deviation, median and interquartile range, or rate and percentage. Univariate statistical analysis will be performed using the Student’s *t* test for parametric continuous variables, the Wilcoxon rank-sum test for non-parametric continuous variables, and Fisher’s exact test for categorical variables. A *p* value < 0.05 will be considered statistically significant.

Subsequently, clinical characteristics which are most likely associated with BPD or death will be included in a multiple logistic regression analysis to assess their independent role in predicting clinical outcome. Effect estimates will be expressed as odds ratios (ORs) with maximum likelihood-based 95% confidence limits.

The primary statistical analyses will be performed according to the intention-to-treat principle. The per-protocol analyses will be also performed with an explanatory intent. Major protocol deviations will be reported. Patients without any information available about the primary study endpoint will be classified as failure. Single imputation will be used in case of missing values will be observed for the covariates included in the adjusted and subgroup analyses.

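### The limits 0.41 and 0.8 for enlarging the trial are printed as Z values but appear to be conditional powers, so the rule as printed enlarges the wrong interim results; rule 3 also overlaps the two stopping rules

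*Protocol article*

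**What the plan says.** The Sample size section of the protocol article plans one interim analysis after 167 infants per arm (334 of 668) and gives four numbered rules. All four are stated on the value of the Z test:

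- Rule 1: if it "gives a value equal to or less than 0.01, the study will be terminated for futility".
- Rule 2: at 2.75 or more, the trial stops for efficacy.
- Rule 3: if it "gives a value less than 0.41 or higher than 0.8, the study will be continued" to 668.
- Rule 4: if it "gives a value equal to or higher than 0.41 and equal to or less than 0.8", the final sample size is changed, up to 1.5 times the planned size (1002).

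No order of precedence is given. The Additional analyses section says that the interim covers efficacy, safety, futility and, if needed, a sample-size adjustment, but it names no other scale. The article does not mention conditional power.

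**The concern.** An increase in sample size is normally reserved for interim results that are promising but uncertain. Z between 0.41 and 0.8 at half information is a weak result, well short of the planned effect. The numbers also look odd as Z limits: 0.8 equals the trial's power target, and 0.41 is a familiar size for a conditional-power limit. If the scale is wrong, up to 334 more preterm infants (1002 − 668) would be recruited after weak interim results and none after the results where more infants could decide the trial.

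Rule 3 also has no lower or upper bound. Read literally, it tells the trial to continue at values where rules 1 and 2 tell it to stop.

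**Working it through.** **Inputs from the Sample size section.** Event rates: "Assuming the percentage of newborns with death or BPD is 35% (the most conservative condition) in the control group"; the LUS group is put at 25%. Size: "a sample size of 668 children (334 per arm) is required to obtain a statistical power of 80% with alpha 0.05". Interim at 334/668, so t = 0.5. Cap 1002, so t = 334/1002 = 1/3 after a full increase.

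**Assumptions.** Two-sided 0.05; final critical value 1.96 (not stated; 1.98 changes little); positive Z favours the LUS group; all interim outcomes known; every enlarged trial goes to 1002.

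**The plan's own figure.** Pooled two-proportion formula: n = [1.96·√(2·0.30·0.70) + 0.842·√(0.35·0.65 + 0.25·0.75)]² / 0.10² = 329 per arm, 658 in total. This is within 2% of 668. One-sided variants give 514 to 558, so the two-sided reading is the right one.

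**What the printed limits mean.** Observed difference = Z·√(2·0.30·0.70/167) = Z × 5.01 points. Observed-trend conditional power (CP) = Φ[(Z/√t − 1.96)/√(1−t)]. For the planned effect, the drift at 668 is 0.10/√[(0.2275 + 0.1875)/334] = 2.84.

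| Interim Z | Difference (points) | Trend CP, 668 | Trend CP, 1002 | Planned-effect CP, 668 | Planned-effect CP, 1002 |
|---|---|---|---|---|---|
| 0.41 | 2.1 | 2.5% | 6.3% | 36% | 76.6% |
| 0.80 | 4.0 | 12.1% | 24.1% | 51% | 84.2% |
| 1.50 | 7.5 | 59% | 78% | 77% | 93% |

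At Z = 1.50, where an increase would raise trend CP from 59% to 78%, rule 3 holds the trial at 668.

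**Where 0.41 comes from.** Find the interim Z at which going to 1002 leaves the conditional one-sided error of an unadjusted final test unchanged:

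(1.96 − √0.5·Z)/√0.5 = (1.96 − √(1/3)·Z)/√(2/3)

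2.772 − Z = 2.400 − 0.707·Z, so Z = 1.268.

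Trend CP there is 0.407 (0.406 with a final value of 1.98), which rounds to 0.41. Above this point an increase to the cap does not raise the error; below it, it does. The usual upper limit is the target power, 0.80. Both printed numbers are therefore recovered as conditional powers. On the Z scale, CP 0.41 and 0.80 are 1.27 and 1.81, or observed differences of about 6.4 and 9.1 points.

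**How often each zone is reached.** The interim Z has mean 0 under no effect and 2.84·√0.5 = 2.01 under 35% v 25%.

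| Zone | No effect | 35% v 25% |
|---|---|---|
| Z 0.41 to 0.80 (as printed) | 12.9% | 5.9% |
| Z 1.27 to 1.81 (CP 0.41 to 0.80) | 6.6% | 19.0% |

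**Overall error and power.** Integrating over the interim Z, with both stopping rules obeyed and a final test at 1.96:

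| Increase zone | One-sided error | Power |
|---|---|---|
| None | 2.59% | 80.9% |
| As printed | 2.70% | 83.0% |
| CP scale | 2.50% | 83.8% |

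**Overlap.** Z ≤ 0.01 is also below 0.41, so it meets rules 1 and 3. Z ≥ 2.75 is also above 0.8, so it meets rules 2 and 3.

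**The case against.** Four points can be made for the plan.

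- A reader might infer that the printed zone enlarges hopeless trials. That holds only under the observed trend. Under the planned effect, conditional power in the zone is 36% to 51% at 668 and about 77% to 84% at 1002. This stands, and it limits the wording. It does not justify the zone: under either convention, the rule passes over better results and enlarges after worse ones.
- A reader might infer a material loss of error control. The figures do not support that. The printed zone adds about 0.1 point of one-sided error (2.59% to 2.70%); the other excess over 2.5% comes from the 2.75 look. Both assume a 1.96 final test and a full increase every time. The Statistical analysis section names Fisher's exact test for categorical variables, which would bring the overall error to about 2.3%.
- The scale error is an inference. The article does not name conditional power, and the fault may lie in the article and not in the operating protocol, which is not public. This stands. Still, two numbers matching the trial's own inputs are hard to put down to chance, and the article prints a definite scale that must be corrected or defended.
- Rules 1 and 2 come first and say that the trial ends, so a sensible reader would apply rule 3 only to what remains. That reading removes the overlap, and a board is unlikely to continue at Z of 2.75 because of rule 3. The text does not state it, however, so this is a drafting fault that is easily closed.

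**Conclusion.** The point holds as a wrong or unworkable threshold in the interim rules. On the printed Z scale, the increase is about twice as likely when there is no effect (12.9%) as under the planned effect (5.9%). On the conditional-power scale the order reverses (6.6% and 19.0%). The damage is mainly in which interim results lead to more recruitment; overall error and average power (about 83% on either scale) hardly move.

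That 0.41 and 0.8 were meant as conditional powers is strongly supported but not stated in the article. The finding does not depend on it: if Z was intended, the zone still needs a justification that the article does not give. The figures rest on the assumptions listed in the check. The values 0.01 and 2.75 can be genuine Z limits and are not questioned here.

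**What to change.** Amend the interim rules before the interim at 334 infants (213 were enrolled on 25 September 2023):

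1. State 0.41 and 0.8 as conditional power under the observed trend, with the Z equivalents of about 1.27 and 1.81. If Z was intended, confirm and justify it.
2. Restrict rule 3 to results that meet none of rules 1, 2 or 4.
3. State that positive Z favours the LUS group.

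This is a change of wording only. Its price is that an increase becomes more likely if the planned effect is real: about 19% against 6%. If every increase went to 1002, that is on average 334 × (0.190 − 0.059) ≈ 44 more infants under the planned effect, and 334 × (0.129 − 0.066) ≈ 21 fewer under no effect.

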### Randomization

Newborns will be allocated to one of the treatment groups (LUSG or CG) in a 1:1 ratio via a central electronically generated procedure by the e-clintrials platform (https://www.eclintrials.org/ect/) managed by [name]. The researchers will login to the platform using their personal username and password. Then a randomization form will be completed in order to verify the presence of the inclusion criteria and the absence of the exclusion criteria. Once the patient’s eligibility is confirmed, the portal will carry out an automatic randomization. Randomization is stratified by center and gestational age.

A block randomization method will be used to guarantee an adequate sample number even for the lowest GAs (25^+0^ to 26^+6^ weeks or 27^+0^ to 29^+6^ weeks).

A monthly accrual report about the study will be sent to the participating centers.

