### Blinding

This is an open non-blinded study, and the staff performing the study will also take subsequent care of the infants.

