### Intervention

Infants will be allocated in one of the two treatment groups in a 1:1 ratio according to the minimization method, using an interactive web-based electronic system.

Infants will be electronically randomized into two groups:Control group (CG): surfactant administration when FiO_2_ > 0.30 on nCPAP (positive pressure 6–8 cmH_2_0) to maintain preductal SpO_2_ between 90 and 95% [1].LUS group (LUSG): surfactant administration when LUS > 8 on nCPAP (positive pressure 6–8 cmH_2_0) to maintain preductal SpO_2_ between 90 and 95% [1].

The LUSG will receive SRT as rescue therapy in case of LUS ≤ 8 but FiO_2_ > 0.30 on nCPAP (positive pressure 6–8 cmH_2_0) to maintain preductal SpO_2_ between 90 and 95%.

The cut-off of LUS > 8 is in agreement with previous studies [3, 4, 11].

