In conclusion, relying only on the FiO_2_ criterion to guide SRT in neonates with RDS on non-invasive respiratory support may have suboptimal accuracy.

Our hypothesis is that LUS may predict more accurately which preterm infants, assisted in nCPAP for RDS, may benefit from early surfactant administration. Instead of evaluating only the oxygen requirements, the use of semi-quantitative LU allows quantification of RDS severity in a score (LUS). LUS estimates the degree of lung aeration or lung recruitment, which reflects the amount of alveolar surface available for gas exchange. This hypothesis was confirmed by the ULTRASURF study [4]. The authors showed that patients randomized to SRT based on LUS received earlier treatment and with lower oxygen requirements compared to neonates who received SRT according to FiO_2_ value. However, the study has several limitations, such as the relatively small sample size, the moderate prematurity of studied infants, and the single center study design.

Therefore, we designed a study which overcomes these limitations. Specifically, we aimed to recruit a large cohort of patients and calculate a sample size powered to demonstrate an improvement in the composite clinical outcome of BPD or death; we stratified the recruitment for gestational age to include an adequate proportion of extremely preterm neonates; and we included several centers in different European countries to allow for an improved generalizability of the study results.

All the participating centers have considerable experience in LU, LUS calculation, and non-invasive respiratory support. Moreover, in the preliminary meetings, we discussed respiratory management during the first hours of life and reached a consensus in order to uniform and standardize the respiratory management among the participating centers as much as possible to limit possible sources of bias.

There are some limitations in our study design. First, the participating centers adopt different methods of surfactant delivery: LISA, INSURE, and IN-REC-SURE. Second, once the patient has received SRT, different respiratory strategies and devices are used to deliver non-invasive respiratory support among participating centers. However, although there is variability between centers, the same protocol is adopted within the center. Since we randomize on center, this is likely not to affect the differences between the two groups within the center.

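### The article names two incompatible allocation algorithms, and credits allocation with securing enough of the youngest infants, which it cannot do

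*Protocol article*

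**What the plan says.** The Randomization section of the protocol article gives a 1:1 allocation: "Newborns will be allocated to one of the treatment groups (LUSG or CG) in a 1:1 ratio via a central electronically generated procedure". It names the factors: "Randomization is stratified by center and gestational age". It then names the method and its purpose: "A block randomization method will be used to guarantee an adequate sample number even for the lowest GAs". The parenthesis after that sentence lists both gestational-age groups, 25+0 to 26+6 and 27+0 to 29+6 weeks, which together make up the whole eligible range.

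The Intervention section describes the same step differently: "Infants will be allocated in one of the two treatment groups in a 1:1 ratio according to the minimization method", through a web-based electronic system.

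The Discussion returns to gestational age as one of the ways the trial improves on an earlier single-center study: "we stratified the recruitment for gestational age to include an adequate proportion of extremely preterm neonates". It also relies on center as a factor: "Since we randomize on center, this is likely not to affect the differences between the two groups within the center".

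Under Statistical analysis, the only test assigned to categorical variables is Fisher's exact test. A multiple logistic regression follows. Its covariates are the clinical characteristics most likely to be associated with BPD or death, and the randomization factors are not named among them.

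**The concern.** There are two separate faults.

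First, stratified permuted blocks take the next assignment from a list prepared for each stratum, whereas minimization computes it from running totals over the factors. A reader cannot tell from the article which one produced the allocation. This is a basic item in the report of any randomized trial. It matters more here because treatment is open: "This is an open non-blinded study, and the staff performing the study will also take subsequent care of the infants". How far local staff could anticipate the next assignment depends on which algorithm is running.

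Second, a property is claimed that the design does not have. Readers told that the number or proportion of the youngest infants is secured by the allocation method may take representation of that group as settled, when the stated mechanism has no bearing on it.

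An analysis issue follows. Allocation is balanced on center and gestational age, and the Discussion leans on the balance within centers. The only test given for the primary outcome ignores both factors. When arms have been balanced on factors related to outcome, an unadjusted test tends to be conservative and gives up some of the precision that the balancing was meant to provide.

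**Working it through.** **1. Are the two descriptions about the same step?** Both concern the same infants, the same two arms, a 1:1 ratio and an electronic central system. The article does not assign one method to an earlier stage, an earlier protocol version or a subset of centers. They are therefore two descriptions of one step, and they conflict.

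**2. Can allocation set the size of a gestational-age group?** The Randomization section puts the order as: form completed, eligibility confirmed, then automatic randomization. Gestational age is fixed before the assignment is drawn. If q is the share of enrolled infants under 27 weeks, the expected number in that group is 668 × q whatever the algorithm: 668 × 0.10 = 67, 668 × 0.20 = 134, 668 × 0.30 = 200, 668 × 0.40 = 267.

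**3. Simulation.** Inputs from the article: 668 infants, the 19 listed centers and two gestational-age groups. Assumptions, because the article gives no values: q from 10% to 40%, unequal center sizes drawn between 10 and 70 and then rescaled, blocks of 4, minimization on center and gestational age with a biased coin of 0.8, and 300 runs per setting.

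| Assumed share under 27 weeks | Mean number in group: simple / blocks / minimization | Mean absolute difference between arms in that group: simple / blocks / minimization |
|---|---|---|
| 10% | 67 / 66 / 67 | 7.0 / 3.2 / 1.1 |
| 20% | 133 / 133 / 133 | 9.7 / 3.1 / 1.1 |
| 30% | 200 / 200 / 201 | 11.1 / 3.4 / 1.2 |
| 40% | 266 / 268 / 268 | 12.4 / 3.0 / 1.2 |

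The middle column varies only by simulation noise, as it must, because gestational age is drawn before allocation. The right-hand column shows what the algorithm does control: balance between the arms among infants already enrolled.

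**4. Does this disturb the stated sample size?** Inputs from the Sample size section: 35% versus 25%, 80% power, alpha 0.05 (two-sided assumed), 334 per arm. With the pooled-variance formula,

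n per arm = [1.96 × √(2 × 0.30 × 0.70) + 0.842 × √(0.35 × 0.65 + 0.25 × 0.75)]² / 0.10² = 329,

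or 658 in total. The article's 668 is 1.5% above this, and power at 334 per arm is 80.7%. The stated figure reproduces, and none of its inputs depends on the allocation algorithm.

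**The case against.** **The factors are the same either way.** The Randomization section names center and gestational age, and the Intervention section names no others, so an adjusted analysis would use the same covariates under both methods. Allocation is central under both. Block size or the random element of a minimization can properly sit in the full protocol and be withheld from sites. All of this stands: the contradiction does not make the trial invalid, and no missing detail of that kind is held against it.

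**The guarantee may be clumsy wording for comparable arms within each group.** The parenthesis listing both groups lends this some support. The Discussion weakens it, because it speaks of the proportion of extremely preterm infants included, and offers this as an answer to the moderate prematurity of the earlier study. On either reading the sentence needs correcting.

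**A recruitment target may exist in the full protocol.** It may, and its absence from an article is not a fault. The point is narrower: the mechanism the article states cannot deliver the purpose it states.

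**A reader might infer that the trial is at risk of being underpowered**, because gestational-age mix, and with it the 35% control rate, is left to accrual. The documents do not support that. They give no event rates or shares by gestational-age group. Suppose assumed risks of 60% and 24.3%, and a younger share of 15% instead of 30%. The control rate falls to about 30%, and power falls to 71% if the relative reduction is held. Hold the 10-point difference instead (29.6% versus 19.6%, 334 per arm) and power is about 85%, above the planned figure. The direction thus depends on a choice the article does not make. The 35% also comes from the participating centers' own data, which presumably reflect case mix as it arises there.

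**Conclusion.** The point holds as two errors of statement plus one improvement to the analysis. Two current sections name incompatible algorithms for one allocation step. The Randomization section and the Discussion credit allocation with securing the number or proportion of the youngest infants, which allocation after confirmed eligibility cannot do. These conclusions rest on the text alone. The simulation only illustrates the second, and its shares, block size and coin probability are assumptions.

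The size is modest. The trial remains valid under either algorithm, the 668 reproduces, and no change in control rate or power is claimed. The precision lost by an unadjusted primary test cannot be quantified from the article. A statistical analysis plan that is not shown may already provide for adjustment; the article as written does not.

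**What to change.** 1. In both the Randomization and Intervention sections, name the one algorithm that the web platform runs, with center and gestational-age group (25+0 to 26+6, 27+0 to 29+6 weeks) as its factors. This corrects the description and does not call for a change to the running system. At the status date, 213 of 668 infants had been enrolled.

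2. In the Randomization section and the Discussion, replace the wording about an adequate number or proportion with a statement that the method balances the arms within gestational-age groups.

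3. Under Statistical analysis, make the primary BPD-or-death comparison adjusted for, or stratified by, gestational-age group and center, for example by logistic regression or a Mantel-Haenszel analysis. Because some centers are expected to be small ("We estimate that the participating centers will have a minimum of 10 and a maximum of 70 eligible patients during the study period"), state beforehand that small centers are pooled or that center enters as a random effect. Fisher's exact test can stay as a supporting analysis.

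Items 1 and 2 cost only wording. Item 3 uses factors already recorded at randomization and needs no further data or infants; it should be fixed before any comparison by arm is seen, including the interim analysis.
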